### External facilitation

Our experience and the literature have shown that coupling training with a site implementation strategy optimizes the benefits of EBP training. External facilitation increases providers’ success in bringing their new skills into their particular clinical setting [18, 21–23]. All enrolled mental health providers (regardless of randomization) will receive external facilitation. Facilitation is a dynamic, individualized process that typically bundles other implementation strategies [36]. For this project, external facilitation will include resolving implementation barriers, training and consultation, and technical support for the CALM tool. This study design feature will allow us to use an evidence-based strategy for implementing CBT while also determining whether CALM or manualized CBT results in improved fidelity to the treatment model. The external facilitator (an individual not located at the implementation site but who has knowledge and experience with VA practices and procedures) will help each provider develop an implementation plan, including setting individual goals for CBT implementation and helping to resolve barriers that emerge to implementing CALM (computer tool or manual). The facilitator will be present at the training sessions to meet the providers face-to-face. Thereafter, the facilitator will meet by phone with each therapist at least once a month for 3 months and be available on an “as-needed” basis for an additional 3-month period [21]. Monthly calls between the facilitator and mental health provider will differ from consultation by focusing on developing a plan to implement the CBT delivery method (e.g., how to use CALM or manual in session), generating solutions to barriers to CBT implementation (e.g., scheduling, time management), and maintaining motivation to practice CBT and the assigned delivery method.

### Training and consultation

All providers will receive training in CBT. The training will be of the same length and format (3-day, face-to-face) as initial training programs in VA rollouts of EBPs [37]. The training will differ across the two groups (those randomized to receive the CALM tool versus manual) in that the final 2 h of each day will involve practice with either delivery method. All providers who complete the training (regardless of randomization) will receive consultation for 3 months, which will consist of small group discussion with “audit and feedback” reports to therapists. Consultation will focus on coaching and giving providers feedback on the delivery of CBT. Both elements have been shown to be important in ensuring proficient delivery of EBPs [38]. Providers will audiotape all of their clinical sessions, and the consultant will review a sample of audiotapes from their sessions during the first 3 months. The consultant will review all recordings from the providers’ first patient and will provide written (via e-mail) or oral (via telephone) feedback after the second and last sessions. If a provider appears to need additional instruction, the supervisor will provide weekly individual consultation over the telephone for the provider until both agree that any problems have been resolved.

### Technical assistance for the CALM tool

Providers randomized to receive the CALM tool will receive ongoing technical support by phone. A technical support specialist will check in weekly with each provider using the CALM tool during the first month and will troubleshoot any problems that emerge. Thereafter, the technical support specialist will check in monthly but will also be “on call’ to address any technical challenges to using the CALM tool.

### Data collection

#### Fidelity assessments

Fidelity to the CBT model will be the primary outcome. Consistent with the recommendations [39], a multidimensional approach to measuring fidelity will be taken. We will use the fidelity rating scales employed in the prior CALM study in which fidelity is rated on a 1 to 7 scale using multiple items spanning three domains: protocol adherence, protocol competence, and global competence. Although separate ratings will be completed for each of these three domains, they will ultimately be combined to create a single measure of fidelity. We will add a fourth domain (non-adherence) developed just for this study. We believed this additional measure would be useful in identifying incidents of serious non-adherence to the CBT model which is associated with poorer treatment outcomes [40].

#### Fidelity rater selection, training, and procedures

Raters will be doctoral level CBT experts who either attend or review an audio recording of the training workshop for study therapists. They will also be provided with the treatment manual. To establish initial inter-rater reliability, each of two raters will independently rate an audiotape of a session and share his/her item-by-item ratings to determine a consensus rating for each item when discrepancies are found. This procedure will be repeated for a minimum of five sessions and until two consecutive sessions have a percentage of agreement on items of ≥80 % for the initial ratings.

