#### Fidelity ratings

Fidelity assessments will focus on therapy sessions delivered early and late in the project. Fidelity for the first patient will be assessed and used to control for initial group differences in multivariate analyses. We expect each therapist to see ten patients each, with each patient completing up to eight sessions. Fidelity will be assessed only for patients who have attended at least four sessions. Fidelity will be measured for a “midpoint” patient (patient four or five of ten) and the last patient receiving at least four treatment sessions from each therapist. Fidelity for the midpoint and last patient for each therapist is our primary outcome measure. A single overall fidelity rating will be completed for each (midpoint and last) patient’s last three sessions. A minimum of 5 % of the total sessions being analyzed will be randomly selected to be rated by both raters to characterize inter-rater reliability.

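### Raters of the subjective primary outcome may attend a workshop that differs by arm, so they can learn a provider's arm before scoring

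*Protocol article*

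**What the plan says.** All references are to Aim 2 of the Protocol article.

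- **Outcome.** Fidelity Assessments: "fidelity is rated on a 1 to 7 scale using multiple items spanning three domains". Fidelity ratings makes the scores for each provider's midpoint and last patient the primary outcome. It also has the first patient rated, to adjust for initial differences between groups.
- **Raters.** The section on rater selection and training describes who they are and how they prepare: "Raters will be doctoral level CBT experts who either attend or review an audio recording of the training workshop for study therapists".
- **Workshop.** Training and consultation describes three days of face-to-face teaching and says of it: "The training will differ across the two groups". The difference is that "the final 2 h of each day will involve practice with either delivery method".
- **Reliability safeguards.** In calibration, "each of two raters will independently rate an audiotape of a session". The raters then agree a consensus on discrepant items, for at least five sessions and "until two consecutive sessions have a percentage of agreement on items of ≥80 % for the initial ratings". During the study, "A minimum of 5 % of the total sessions being analyzed will be randomly selected to be rated by both raters".

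The article does not say that raters are masked to provider or arm, that they stay away from the arm-specific hours, or which rater scores which recording.

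**The concern.** The randomised contrast is tool versus manual, and the arm-specific part of the workshop is practice with one or the other. A rater in the room for it sees the allocation itself and meets the people to be rated. The same rater may later judge recordings of those people, including their competence, in a trial whose stated hypothesis favours the tool. Having met the providers, the rater may also recognise a voice, so removing names from the files would not fully undo the exposure.

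If knowledge of the arm shifts the scores, the shift goes straight into the treatment difference. A larger sample would not remove it. It has to be prevented before the ratings are made.

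**Working it through.** **1. Is the route to unmasking stated or inferred?** Two statements combine. Raters may attend the workshop. The workshop differs by arm in the last 2 h of each of 3 days, which is 3 × 2 = 6 h of arm-specific practice. The permission to attend is explicit. That a rater would be present in those 6 h is not stated, but nothing excludes it.

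**2. Inputs for scale** (Power analysis): 30 providers after losses, so 15 per arm; planned difference 1.2; SD 1.2. The test level of 0.05 is from Data analysis.

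**3. The plan's own figure.** The article states 84 % power, two-tailed. The standard error of the difference is 1.2 × √(2/15) = 0.438, so the noncentrality is 1.2 / 0.438 = 2.74. At two-sided 0.05 with 28 degrees of freedom this gives 75.3 % (noncentral t) or 78.2 % (normal approximation). One-sided 0.05 gives 84.8 %, and the printed alpha of 0.5 gives 98.0 %. So 84 % does not reproduce as a two-tailed 0.05 test. That is a separate matter. Only the sample size and SD are used below.

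**4. Arm-related rating shift.** Suppose there is no true difference and ratings in one arm are shifted by b. The noncentrality is b / 0.438, and type I error is the chance that the two-sided t-test rejects. Every b is an assumption, since the document gives none.

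| Assumed b (points) | b / 1.2 | Type I error |
|---|---|---|
| 0 | 0 % | 5.0 % |
| 0.1 | 8 % | 5.6 % |
| 0.2 | 17 % | 7.3 % |
| 0.3 | 25 % | 10.1 % |
| 0.5 | 42 % | 19.7 % |

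These are for an unadjusted comparison. If the same shift also raises the first patient's score, and that score enters as a covariate with slope β, the adjusted difference carries b − βb = b(1 − β), which is smaller than b for β between 0 and 1.

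**5. Rater severity.** A constant gap s between the two raters biases the comparison only if their recordings are unevenly spread: bias = s × (difference between arms in the share scored by the harsher rater). With s = 0.5 (assumed):

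- 50/50 in both arms: bias 0, type I error 5 %.
- 60/40 against 40/60: 0.5 × 0.20 = 0.10, giving 5.6 %.
- 67/33 against 33/67: 0.5 × 0.34 = 0.17, giving 6.6 %.
- One rater per arm: 0.5, giving 19.7 %.
- One rater per provider, assigned at random: no bias. The variance becomes 1.44 + 0.5²/4 = 1.5025 (SD 1.226), and power falls from 75.3 % to 73.5 %.

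**6. Double-rated overlap.** For the midpoint and last patients, 30 × 2 × 3 = 180 sessions, of which 5 % is 9. If the rated unit is the patient, 60 × 5 % = 3. Either is too few to estimate or correct a severity gap with any precision.

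**The case against.** **The route is only permitted.** Attendance is one of two options, and the article does not say that both arms share one workshop or that raters stay for the practice hours. This stands. A reader might infer that raters will know every provider's arm, and the text does not support that. It supports only that they can.

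**The article condenses a fuller protocol.** This would answer a complaint that masking is not mentioned. It does not answer a stated procedure that opens a way to unmasking.

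**Raters are calibrated.** The requirement of at least 80 % item agreement is a real safeguard against raters diverging from each other. It does not protect against both raters knowing the arm.

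**Rater severity.** A reader might infer that severity is unbalanced between arms. The article is silent on allocation, so this cannot be claimed, and step 5 shows that random allocation would make it a minor matter. Nor can it be said that giving each rater one of a provider's two outcome patients removes severity altogether. It cancels a constant additive gap in the mean of the two scores, (s − s)/2 = 0, when both patients are rated. Severity can still enter through the first patient's score used as a covariate.

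**Session audio may reveal the arm anyway.** The CALM program section says that patient and provider work from the screen together in the tool arm. This stands, so attendance may add only part of the total unmasking, and that part cannot be estimated from the document. It is still the part that can be avoided at almost no cost.

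**Conclusion.** The point holds as an avoidable weakness in how the primary outcome is measured. The article permits raters to be present at training that differs by arm, the outcome is a judgement, and no described safeguard addresses knowledge of the arm.

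The size is unknown. Assumed shifts of 0.1 to 0.5 points correspond to type I error of about 5.6 % to 20 %, given 15 providers per arm, SD 1.2, a two-sided 0.05 t-test and no adjustment. With the first-patient covariate the effect would be smaller to the extent that the covariate carries the same shift. The range shows what is at stake and does not predict the bias. Rater allocation is a precaution here, not the correction of a stated error.

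**What to change.** 1. Train raters only from a recording of the CBT content common to both arms, with no attendance in person and no exposure to the arm-specific practice hours. The article already accepts audio-only training, but limiting the recording to common content is a new restriction.
2. Give raters session recordings under a code, without provider name or arm.
3. Allocate the recordings of the first, midpoint and last patients to the two raters at random, balanced by arm. For example, give a provider's midpoint patient to one rater and the last patient to the other, alternating the order within arm, and balance the first-patient recordings by arm as well.
4. State the raters' masking status, and acknowledge that session audio may disclose use of the tool.

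The cost is editing one recording, coding files and keeping an allocation list. No extra raters, ratings or providers are needed. Raters lose live attendance, which is already optional, and masking remains incomplete.

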#### Fidelity ratings

Fidelity assessments will focus on therapy sessions delivered early and late in the project. Fidelity for the first patient will be assessed and used to control for initial group differences in multivariate analyses. We expect each therapist to see ten patients each, with each patient completing up to eight sessions. Fidelity will be assessed only for patients who have attended at least four sessions. Fidelity will be measured for a “midpoint” patient (patient four or five of ten) and the last patient receiving at least four treatment sessions from each therapist. Fidelity for the midpoint and last patient for each therapist is our primary outcome measure. A single overall fidelity rating will be completed for each (midpoint and last) patient’s last three sessions. A minimum of 5 % of the total sessions being analyzed will be randomly selected to be rated by both raters to characterize inter-rater reliability.

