### Aim 2: hybrid type III study

Our second aim we will be to use a hybrid type III [35] study design to conduct an RCT comparing the effect of a modified CALM tool versus that of a manualized version of CALM on our primary outcome—CBOC mental health provider fidelity to CBT. A hybrid III study design was used given (a) a substantial and clear evidence base indicating improved clinical outcomes associated with patients receiving CALM; (b) a strong need to identify optimal delivery methods for implementing CBT in VA CBOCs; and (c) the fact that CALM has significant “implementation momentum” [35] as our VA Central Office research partners are interested in adapting the CALM tool for use in VA CBOCs. Mental health providers will be randomized to receive CBT training plus the CALM tool or a manualized version of CALM. We hypothesize that providers randomized to receive CBT training and the CALM tool will demonstrate higher treatment fidelity than providers receiving the manual. We also hypothesize that veteran patients of providers randomized to receive CBT training and the CALM tool will have clinical outcomes superior to veteran patients of providers who receive the manual.

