### Study participants

Participants will include mental health providers and veteran patients. We will recruit 34 mental health providers (all disciplines eligible) to receive training in CBT. Upon completion of training, each mental health provider will invite ten of his/her patients to participate in CBT treatment (Table 1).

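### First-patient fidelity, planned as an adjustment for starting differences, is a post-randomisation outcome; the plan should say it stays out of the primary model

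*Protocol article*

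**What the plan says.** All places are in the protocol article, Aim 2.

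- **Fidelity ratings:** "Fidelity for the first patient will be assessed and used to control for initial group differences in multivariate analyses". The same section makes fidelity with the midpoint and last patients the primary outcome.
- **Aim 2, opening section:** "Mental health providers will be randomized to receive CBT training plus the CALM tool or a manualized version of CALM". The hypothesis there is that tool providers will show higher fidelity than manual providers.
- **Training and consultation:** the three-day training differs by arm, in that "the final 2 h of each day will involve practice with either delivery method". In the consultation that follows training, "The consultant will review all recordings from the providers’ first patient". This applies to both arms.
- **Study participants:** "Upon completion of training, each mental health provider will invite ten of his/her patients to participate in CBT treatment".
- **Technical assistance for the CALM tool:** "A technical support specialist will check in weekly with each provider using the CALM tool during the first month".
- **Data analysis:** the analysis is labelled intent-to-treat, with the mean of the midpoint and last-patient scores as outcome and an arm indicator as the explanatory variable of interest. It calls for three covariates, chosen among provider characteristics that differ between arms. If none differ, it falls back on two: earlier CBT experience and time in practice. First-patient fidelity is not named. The model named is logistic regression.

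The article describes no fidelity rating before randomisation or before training.

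**The concern.** A covariate that corrects for starting differences must be fixed before assignment can affect it. The first patient is treated by a provider who has been randomised, has practised the assigned method on each training day, and is now using it. Any arm difference in first-patient fidelity can therefore be part of the effect under study, not a chance imbalance at the start.

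Conditioning on such a variable changes the question. The arm coefficient becomes the further difference in later fidelity between providers who had the same fidelity with their first patient. That is not the total effect of being assigned the tool, which is what the hypothesis concerns and what an intent-to-treat label implies. In a trial expecting 30 analysable providers, the change could decide whether the primary comparison succeeds.

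**Working it through.** **Step 1: order of events.** The practice blocks are specific to the assigned method, so randomisation must come before the first of them. Patients are invited only once training is complete. The first patient therefore comes after randomisation and after arm-specific training. Consultation is given to providers who have completed training, and it includes review of the first patient's recordings, which agrees with this order. In the tool arm, the weekly technical calls also belong to the first month. Nothing in the article points to a different order.

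**Step 2: the plan's own power figure.** Inputs from Power analysis: 30 providers (taken as 15 per arm), difference 1.2, SD 1.2, two-tailed. Alpha is 0.05 from Data analysis; Power analysis prints 0.5 for this calculation. The standard error is 1.2 × √(2/15) = 0.438, so the noncentrality is 1.2/0.438 = 2.74. Power is 75.3 % by the t-test on 28 df (78.2 % by the normal approximation). The stated 84 % is not reproduced; that is a separate matter. The unadjusted benchmark below is 75 %.

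**Step 3: what adjustment does.** Two quantities are assumptions, because the article gives neither:

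- f: the share of the 1.2-point effect already present with the first patient.
- r: the within-arm correlation between first-patient fidelity and the composite.

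The SD is taken as 1.2 for both measures, so the within-arm slope equals r. The expected arm difference in the covariate is f × 1.2. The expected adjusted estimate is therefore

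1.2 − r × (f × 1.2) = 1.2 × (1 − r × f).

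The residual SD is 1.2 × √(1 − r²). With n = 15 per arm, the variance of the adjusted estimate is approximately

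residual SD² × [2/n + ((1.2f)² + 2 × 1.44/n) / ((2n − 2) × 1.44)],

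and power follows from the noncentral t on 27 df.

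Example, f = 0.5 and r = 0.5:

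- Estimate: 1.2 × 0.75 = 0.90.
- Residual variance: 1.44 × 0.75 = 1.08.
- Variance of the estimate: 1.08 × [0.1333 + (0.36 + 0.192)/40.32] = 0.159, so the SE is 0.398.
- Noncentrality: 0.90/0.398 = 2.26; power 59 %.

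**Step 4: results over the range.**

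| f | Estimate, r = 0.3 / 0.5 / 0.7 | Power, r = 0.3 / 0.5 / 0.7 |
|---|---|---|
| 0 | 1.20 / 1.20 / 1.20 | 78 / 85 / 95 % |
| 0.25 | 1.11 / 1.05 / 0.99 | 70 / 74 / 84 % |
| 0.5 | 1.02 / 0.90 / 0.78 | 61 / 59 / 63 % |
| 0.75 | 0.93 / 0.75 / 0.57 | 50 / 42 / 36 % |
| 1 | 0.84 / 0.60 / 0.36 | 40 / 27 / 16 % |

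Simulation with 20,000 runs per cell agrees: (f, r) = (0, 0.5) gives 1.20 and 85 %; (0.5, 0.5) gives 0.90 and 59 %; (1, 0.5) gives 0.60 and 27 %; (1, 0.7) gives 0.36 and 16 %.

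If the tool lowers fidelity at first, the sign reverses. With f = −0.25 the estimate is 1.2 × (1 + 0.25r), which is 1.29 at r = 0.3 and 1.41 at r = 0.7.

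**The case against.** Four objections carry weight.

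1. **The covariate's place in the primary model is not settled.** Fidelity ratings speaks only of multivariate analyses, and the section that specifies the primary model does not name first-patient fidelity. A reader might infer that the primary estimate is certainly affected, or that this rating is the third covariate which the fallback leaves unnamed. The article says neither. This stands, and it makes the point conditional. It does not remove it: the intended use is stated outright, in the section that defines the primary outcome.

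2. **The loss may be small.** Nothing in the article sets a lower limit on f. Technical problems in the first month, and equally close review of the first patient in both arms, make a small early effect conceivable. At f = 0 adjustment is unbiased and raises power. At f = 0.25 power is 70 to 84 %, close to or above the unadjusted 75 %. This stands as to size. Even so, the estimate at f = 0.25 is 8 to 18 % too low, so what is estimated has changed although power has not suffered much.

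3. **The direction is not fixed.** It is tempting to say that adjustment always pulls the estimate towards zero. That needs both f and r to be positive. A positive f follows the direction of the article's hypothesis, but the article does not establish it for the first patient.

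4. **The figures come from a linear model,** while Data analysis names logistic regression. They illustrate size only. The argument about timing does not depend on the model.

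A reader might also infer that coaching on the first patient distorts the comparison further. The article gives that review to all providers whatever their arm, so it does not by itself create a difference between arms.

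**Conclusion.** The point holds in conditional form. On the article's own sequence, first-patient fidelity is an early post-randomisation outcome, and describing it as a control for starting differences is wrong. Fidelity ratings and Data analysis do not agree on whether it is a covariate and must be reconciled. If it enters the primary model, the coefficient matches neither the hypothesised total effect nor the intent-to-treat label, unless the tool has no effect at the first patient or the correlation is zero.

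Under the stated linear-model assumptions, with r from 0.3 to 0.7, the consequence runs from no bias with some gain in power (f = 0) to an expected estimate of 0.84 to 0.36 points with power 40 to 16 % (f = 1). The documents do not show where in that range the trial would lie. The timing is certain; the size is not.

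**What to change.** State in both Fidelity ratings and Data analysis that first-patient fidelity is not a covariate in the primary model. Adjust only for variables fixed before randomisation; earlier CBT experience and time in practice are already named. Report first-patient fidelity by arm as an early outcome, or use it in an analysis labelled exploratory. Bring the covariate count in Data analysis into line with the variables listed, without filling the third place with this rating.

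The cost is about one sentence in each section. The ratings are still made and used. The downside is that if the tool has almost no effect at the first patient, some precision is given up: at f = 0, power would be 75 % instead of 78 to 95 %.

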### Data analysis

Providers will be the unit of the intent-to-treat analysis for measuring our primary (fidelity to the CBT model) and secondary (mental health) outcomes. For our primary outcomes, the dependent variable will be the composite fidelity score from each provider’s midpoint and last patient. The composite score will be calculated as the mean of the two scores. A dummy variable representing treatment group assignment will be specified as the explanatory variable of interest. An alpha significance level of 0.05 will be used to reject/accept the null hypothesis. Study hypotheses will be tested using a standard logistic regression model. Three covariates will be specified to control for differences across providers. We will first examine differences in the characteristics of providers across the intervention and control group and include those characteristics that differed statistically. If no group differences are observed in the characteristics of the providers, we will control for previous CBT experience (none, some, most experience) and length of time in clinical practice. To examine our secondary outcomes, overall mental health functioning will be measured at baseline and at 3 and 6 months follow-up. Patients will also be screened for any of five specific disorders at baseline (PTSD, PD, GAD, SAD, and comorbid depression); and for those who score positive in a given disorder, ongoing assessment of that disorder will continue through the study. We expect a high degree of comorbidity, so participants will choose the disorder that is bothering them the most as the “target” disorder for CBT treatment.

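### The patients on whom randomised providers are scored are chosen with the arm known and filtered by a four-session rule, and the planned covariates do not correct for this

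*Protocol article*

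**What the plan says.** All places are in the Protocol article, Aim 2 unless stated.

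- **Unit and order of events.** The Aim 2 introduction says: "Mental health providers will be randomized to receive CBT training plus the CALM tool or a manualized version of CALM". Under Training and consultation, part of each training day is practice with the assigned method, so a provider knows the arm by the end of training. Study participants then says that, once training is complete, "each mental health provider will invite ten of his/her patients to participate in CBT treatment".
- **Who can be invited.** Table 1 limits invitations to the provider's own patients. Some criteria depend on judgement, such as intending to stay in mental health care and wishing to have CBT.
- **Who is scored.** Fidelity ratings says: "Fidelity will be assessed only for patients who have attended at least four sessions". The midpoint patient is number four or five of ten. The other rated patient is "the last patient receiving at least four treatment sessions from each therapist". The same section says: "Fidelity for the midpoint and last patient for each therapist is our primary outcome measure".
- **Analysis.** Data analysis says: "Providers will be the unit of the intent-to-treat analysis". The composite is the mean of the two scores. Covariates are provider characteristics that differ between arms or, failing that, prior CBT experience and time in practice. Fidelity ratings adds first-patient fidelity as a control for initial differences.

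**The concern.** Randomisation makes the two groups of providers comparable. It does not do so for the patients through whom they are observed, because two selection steps come later. The first is invitation by a provider who knows the arm. A provider with the tool may, knowingly or not, approach different patients from one with the manual. The second is retention to four sessions, which the delivery method may itself affect and which may go with how well the sessions run.

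If either step works differently by arm, a difference in the fidelity score mixes an effect on provider behaviour with a difference in the patients scored. Arm-aware invitation also reaches the patient-level clinical outcomes, for which Aim 2 states a superiority hypothesis.

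**Working it through.** **1. Do the planned controls remove the selection?**

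- The covariates in Data analysis describe providers, not the patients they invited or kept.
- First-patient fidelity is measured after randomisation, after arm-specific training and, on a plain reading, under the same four-session rule. It is not a pre-randomisation baseline.
- Power analysis expects little patient drop-out because a full eight-session course is not needed for inclusion in the study. Being scored still needs four sessions.

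**2. Size of the threshold effect (illustration).** The article has no figure of its own here to reproduce.

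Inputs from Power analysis: difference 1.2 points, SD 1.2 (effect 1.0 SD), 30 providers. Assumptions not in the documents: equal arms of 15, the share p reaching four sessions in each arm, and a positive correlation ρ between a patient's tendency to stay and that patient's fidelity score.

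If patients above a normal threshold are kept, the mean score of those kept is raised by ρ·λ(p) SD, where λ(p) = φ(z_p)/p. The bias is ρ·[λ(p_tool) − λ(p_manual)].

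| p | λ(p) |
|---|---|
| 0.90 | 0.195 |
| 0.80 | 0.350 |
| 0.65 | 0.570 |
| 0.60 | 0.644 |

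- Tool 80%, manual 65%: 0.350 − 0.570 = −0.220. Bias −0.066 SD at ρ = 0.3 and −0.110 SD at ρ = 0.5.
- Tool 90%, manual 60%: 0.195 − 0.644 = −0.449. Bias −0.135 SD at ρ = 0.3 and −0.224 SD at ρ = 0.5.

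Multiplied by 1.2, the range 0.066 to 0.224 SD is about 0.08 to 0.27 points. The arm that keeps fewer patients has the more selected scores and gains. The signs above follow only from assuming that the tool keeps more; swapping the rates reverses them.

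**3. Allowing for variance between providers.** The formula places all the variance at patient level. If half lies between providers, each figure is multiplied by √0.5 = 0.707, which gives 0.047 to 0.159 SD.

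A simulation on that basis (no true effect, 15 per arm, SD 1.2, 4,000 runs per setting) gave:

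| Retention in the two arms | ρ | Bias in points, favouring the lower-retention arm | Rejection rate at nominal 5% |
|---|---|---|---|
| 60% and 60% | 0 to 0.7 | about 0 | 5% |
| 80% and 60% | 0.3 to 0.7 | 0.08 to 0.18 | 5% to 8% |
| 90% and 50% | 0.3 to 0.7 | 0.15 to 0.36 | 7% to 15% |

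With ρ = 0 the bias was about zero at every pair of rates.

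**4. Scale.** With 15 per arm, the standard error of the difference is √(2/15) = 0.37 SD. A bias of 0.07 to 0.11 SD is under a third of that; 0.22 SD is about 0.6 of it.

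The effect of arm-aware invitation cannot be put into figures from the article.

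**The case against.** The strongest reply is that providers are both the randomised and the analysed unit, the outcome is provider behaviour, and patients are only occasions for sampling it. Fidelity once a ratable amount of CBT has been given is a legitimate target, and rating a patient's last three sessions needs some minimum. Both arms deliver CALM content with the same facilitation and consultation, so retention may well be equal, and then the threshold does no harm. Much of this stands. It is why the four-session rule can remain in the primary analysis. It does not answer invitation with the arm known, and equal retention is a hope that the trial should check.

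Three stronger readings are tempting, and the article does not support them:

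- **That the intent-to-treat claim is false.** Nothing says that a provider is moved between arms or removed. How a provider with one or no scorable patient is handled may be in an analysis plan that is not shown.
- **That a provider with fewer than four retained patients has no midpoint score.** The plan says "We expect each therapist to see ten patients each, with each patient completing up to eight sessions", and the midpoint is number four or five of those ten. A provider with three retained patients, one of them the fourth, has a midpoint score. What is left open is which to rate when both qualify.
- **That the tool is known to retain better.** The CALM program section reports substantial engagement with the tool in one study, but gives no manual comparator.

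Scoring everyone regardless of attendance in the primary analysis is also not clearly better. The arm with poorer retention would then be rated more often on early sessions, whose content may differ from later ones.

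**Conclusion.** The point holds as a weakness in design. Patients are invited with the arm known, the primary score is confined to those who reach four sessions, and no planned covariate corrects for either step. Bias from the threshold needs retention, or its link to fidelity, to differ by arm. Since neither is given, its size and direction are unknown. Under the assumed rates and correlations it is 0.07 to 0.22 SD, roughly 7% to 22% of the planned effect, and about 0.05 to 0.16 SD if half the variance lies between providers. That would not by itself overturn an effect as large as the one planned, but it would matter for a moderate one. The change is worth making because it is cheap, and because selection at invitation cannot be undone once patients are enrolled.

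**What to change.** 1. **Invitation.** Each provider lists eligible patients before the arm is disclosed, hence before arm-specific training, and invites them in list or appointment order. Invitations and refusals are logged. Cost: a short log; the list may go stale and should then be refreshed by the same order rule.
2. **Midpoint patient.** Study staff, not the provider, choose from the enrolment log in a fixed order: patient 5 if scorable, otherwise patient 4. Cost: negligible.
3. **Threshold.** Keep the four-session rule for the primary analysis and report by arm the share of patients reaching four sessions. Add a sensitivity analysis that rates the midpoint patient and the last enrolled patient with any recorded session, whatever the number attended. Cost: some extra ratings, and short courses are harder to score on some items. No new recording is needed, because Training and consultation already has providers audiotape all their clinical sessions.
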